## Abstract

**Introduction:**

Spinal cord injury (SCI) is a devastating injury often associated with immobility, leading to numerous complications, with cardiovascular disorders being among the major causes of mortality. Upper-limb aerobic exercise (ULAE) may help to retrain and regain some of the abilities lost through SCI and minimize secondary complications. The purpose of this study is to determine the effects of ULAE plus general exercise compared to the same general exercise on cardiovascular parameters, functional independence, and quality of life among patients with SCI in northern Nigeria.

**Method:**

This is a multicenter, assessor-blind, parallel group, randomized controlled superiority trial to be conducted among SCI patients attending three tertiary hospitals in Kano State, northern Nigeria. Participants fulfilling the study criteria will be randomized into either ULAE (arm ergometer and overhead pulley exercises) plus general exercise group or general exercise only group. Both groups will receive their respective interventions three times per week for 8 weeks. The primary outcomes will be rate pressure product (calculated as systolic blood pressure x heart rate) and functional independence. The secondary outcomes will be blood pressure and quality of life. All outcomes will be assessed at baseline, 8 weeks post-intervention, and at 14weeks follow-up.

**Discussion:**

This study will be the first to determine the effects of ULAE plus general exercise versus general exercise alone among patients with SCI in northern Nigeria. The outcome of this study could provide valuable guidance for rehabilitation professionals in selecting a low-cost and effective intervention for patients with SCI, particularly in resource-constrained settings.

**Trial registration:**

Pan African Clinical Registry (PACTR202306580460880). Registered on June 12, 2023.

## Introduction

Spinal cord injury (SCI) is a devastating injury accompanied by physical, psychosocial, and economic problems, as well as significant personal and social repercussions [1]. It is often associated with distinct diverse secondary complications including acute complications such as bradyarrhythmias, hypotension, impaired temperature, pain, spasticity, and autonomic dysreflexia [2] and chronic complications such as cardiopulmonary, intestinal, urinary bladder, and sexual disorders [3]. Long-term secondary complications can increase morbidity and negatively impact functional independence, community participation, and quality of life (QOL) [3]. Additionally, individuals with SCI, depending on their type of injury, often experience reduced physical activity levels, which is considered antecedent to development of various complications [4]. Individuals with SCI are approximately 40% less physically active compared to able-bodied counterparts [5].

A major complication linked to physical inactivity in individuals with SCI is the increased prevalence and earlier onset of cardiovascular disease (CVD) [6]. Research suggests that individuals with SCI, particularly those with cervical and thoracic levels of injury, often struggle with unstable blood pressure (BP), leading to persistent hypotension and episodes of uncontrolled hypertension [7].

Following SCI, there is an immediate disruption in connections between supraspinal structures and sympathetic preganglionic neurons. This leads to instability, causing spinal circuits to solely regulate sympathetic activity, which impacts BP control. Acute SCI, particularly at the cervical level, often results in severe hypotension and persistent bradycardia, contributing to neurogenic shock. However, the recognition and management of these cardiovascular dysfunctions following SCI pose significant clinical challenges. Moreover, CVD in both the acute and chronic stages of SCI is among the most common causes of mortality in this population [8].

As a greater number of individuals with SCI experience a significant reduction in daily physical activity [9], which increases the risk of secondary health issues and comorbidities post-injury [2,3,10], addressing physical inactivity is a top health care priority [11]. Although exercises such as strengthening and stretching are commonly employed in SCI rehabilitation to improve strength and flexibility, respectively, these exercises are insufficient to address cardiorespiratory fitness. However, one critical intervention to maintain and improve cardiorespiratory fitness and cardiometabolic health, while enhancing upper body strength and endurance, is upper-limb aerobic exercise (ULAE) [12]. Indeed, our Delphi study [unpublished] aimed at identifying the most effective exercise interventions for individuals with SCI in northern Nigeria, suggested a combined arm ergometer and reciprocal pulley exercise program as the most appropriate and cost-effective intervention to improve cardiorespiratory function and functional independence for this population. Moreover, one advantage of this proposed exercise program is that the equipment (arm ergometer and reciprocal pulley) can be improvised and adapted for home use, which is particularly important in resource-constrained settings.

Previous trials evaluating the effects of ULAE for patients with SCI demonstrated promising results in terms of improved pulmonary function [13,14] though failed to show significant effects on functional status, QOL, psychological state, level of disability, and metabolic syndrome [13,14,15], which could be attributed to inadequate sample size and lack of follow-up. Additionally, to our knowledge, no randomized controlled trial (RCT) has been conducted to evaluate the impact of any ULAE program for individuals with SCI in northern Nigeria. Since an ULAE program has been suggested following our Delphi study (unpublished), it is crucial to evaluate its effectiveness to provide recommendations for rehabilitation professionals in our context and beyond. Thus, the purpose of this study is to determine the effects of ULAE plus general exercise program compared to the same general exercise among patients with SCI in northern Nigeria.

We anticipate that ULAE (arm ergometer and reciprocal pulley exercises) combined with a general exercise focusing on strength and flexibility, will significantly improve cardiorespiratory fitness and cardiometabolic health. By enhancing these parameters, the intervention may also contribute to better functional independence, improved QOL, and reduced risk of secondary complications. This could ultimately lead to a reduction in morbidity and mortality rates among this population.

## Methods

### Ethical consideration

Ethical approval was obtained from the ethics committees of Aminu Kano Teaching Hospital (AKTH; Ref: NHREC/28/01/2020/AKTH/EC/3013), Kano State Ministry of Health (Ref: NHREC/17/03/2018), and National Orthopaedic Hospital Dala (NOHD; Ref: NOHD/RET/43). Any protocol amendments will be communicated to the various ethics committee and updated in the Pan African Clinical Trials Registry.

### Objectives

The primary objective is to determine the effects of an 8-week ULAE plus general exercise versus general exercise alone on rate pressure product (RPP) and functional independence among patients with SCI. The secondary objective is to determine the effects of these interventions on blood pressure (BP) (systolic blood pressure [SBP] and diastolic blood pressure [DBP] and QOL.

### Hypotheses

The primary hypothesis is that participants receiving ULAE plus general exercise will demonstrate greater improvements in RPP and functional independence compared to those receiving general exercise alone at 8 weeks post-intervention and at the 14 weeks follow-up. The secondary hypothesis is that participants receiving ULAE plus general exercise will demonstrate greater improvements in BP and QOL compared to those receiving general exercise alone at 8 weeks post-intervention and at the 14 weeks follow-up.

### Study design

This is a multi-center, assessor-blind, parallel group, randomized controlled superiority trial to be conducted among patients with SCI in northern Nigeria. The trial is designed in accordance with the Consolidated Standards of Reporting Trials (CONSORT) guidelines and reported according to the Standard Protocol Items: Recommendations for Interventional Trials (SPIRIT) checklist [16] (see S1 Appendix).

### Study settings

The study is being conducted in the outpatient unit of the Physiotherapy Department at each of the three major healthcare facilities in Kano State, northern Nigeria: AKTH, Murtala Mohammed Specialist Hospital (MMSH), and NOHD.

### Participants

Potential study participants are individuals with SCI who will be identified by consultant spine surgeons and subsequently referred to the physiotherapy outpatient unit. The study flow is illustrated in Fig 1

**Fig 1 pone.0321932.g001:**
[figure not shown]
Flow of participants through the study.

### Inclusion criteria

To be eligible for the study, participants must meet the following criteria:

Received medical clearance from their physicians confirming they are fit to participate in exercise.Male or female aged 18–65 years old.Diagnosed with traumatic SCI between the 7^th^ cervical (C7) and 5^th^ lumbar (L5) vertebrae, with a minimum of 3 months post-injury.Upper limb muscle power of at least 3, as assessed by gross muscle power testing, to be able to propel an arm crank ergometer.Willing to participate and having provided signed informed consent.

### Exclusion criteria

Participants will be excluded from the study if they meet any of the following conditions:

SCI level other than C7 to L5.Presence of serious or unstable cardiovascular or neurological disorders.Brain injury due to trauma.Other secondary health issues (e.g., pressure sores, bladder infections) and medical conditions (e.g., severe psychiatric disease) that prevent participation in physical activities.

### Informed consent

Informed consent will be obtained by the physiotherapist responsible for eligibility assessment after providing participants with a detailed explanation of the study, including its benefits and procedures. Participants will be informed that they have the right to withdraw from the study at any time without any prejudice or negative consequences.

### Sample size calculation

To our knowledge, no previous study has evaluated the effects of ULAE plus general exercise program compared to general exercise alone among SCI patients, using the RPP (product of SBP and HR) as an outcome. However, since the minimal clinically important difference (MCID) for total Spinal Cord Independence Measure III (SCIM III) has been reported to be 10.0 points [17], this study was powered to detect a minimum difference of 10% points between the ULEA group and control group (assuming a standard deviation [SD] of 12.0, based on the study by Akkurt et al. [15]. Using the following parameters— F-test, repeated measures, between-subjects analysis of variance (ANOVA); alpha (*α*) level of 0.05; power of 0.80; effect size of 0.40 when accounting for 3 repeated measures; and correlation among repeated measures of 0.5— a total of 36 participants was required. Accounting for a potential dropout rate of 30% (n = 10), the final sample size was determined to be 46 participants. Calculations were performed using G Power 3.1.9.2 software [18].

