### Randomization and blinding

After ensuring study eligibility and completing baseline assessments, the participants will be randomly assigned to either ULAE plus general exercise group or general exercise alone (control) group. Randomization will be performed by an independent person (a record officer) at each study site using computer-generated random numbers. To ensure allocation concealment, sequentially numbered, opaque, sealed envelopes will be prepared in accordance with the generated random sequence. Upon the availability of an eligible participant at the scheduled appointment, the next envelope will be opened to determine the intervention group to which the participant is allocated. Outcome assessors will be blinded to group allocation. However, owing to the nature of the study interventions, blinding of the physiotherapists administering treatment will not be possible. Unbinding will only be permissible in cases where a participant experiences a serious adverse event or after the study’s completion.

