### Data analysis

All statistical analyses will be conducted on IBM SPSS Statistics version 24.0 (IBM Co., Armonk, NY, USA), with a significance level at 0.05.

Descriptive statistics of means and standard deviations will be used to summarize continuous variables, while frequencies and percentages will be used for categorical variables. Data distribution will be assessed statistically using the Kolmogorov–Smirnov and Shapiro–Wilk tests, and visually through histograms, Q-Q plots, and box plots. Baseline comparisons of continuous variables between groups will be conducted using independent *t-*test while the chi-square (χ²) test will be used for categorical variables. For normally distributed data, a mixed model analysis of variance (ANOVA) with a 2 x 3 design (treatment group [ULAE group versus control group] x time [baseline, 8-week post-intervention, and 14-week follow-up]) will be employed to evaluate treatment effectiveness. The treatment group (between-subject factor) will be treated as a fixed effect, while time (within-subject factor) will be treated as a random effect. For non-normally distributed data, the Mann–Whitney *U* test will be used. Potential confounding variables, such as sex, education level, BMI, duration of injury, and type of injury will be adjusted for in the analysis. The intention to treat (ITT) principle will be applied, with all randomized participants included in the analysis according to their originally assigned treatment groups, regardless of whether they completed treatment.

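### The 80% power for SCIM III belongs to a three-visit group main effect that includes the pre-randomisation baseline; on the protocol's own inputs, neither that term nor the group-by-time interaction has 80% power with 36 participants

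*Protocol article*

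**What the plan says.** In the protocol article, *Sample size calculation* says of the SCIM III total that "this study was powered to detect a minimum difference of 10% points between the ULEA group and control group". The spread behind that target comes from an earlier study and is entered as "assuming a standard deviation [SD] of 12.0". The test is given as "F-test, repeated measures, between-subjects analysis of variance (ANOVA"), with an alpha "level of 0.05; power of 0.80", and "effect size of 0.40 when accounting for 3 repeated measures; and correlation among repeated measures of 0.5". From this, "a total of 36 participants was required"; a 30% dropout allowance raises the target to 46.

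*Data analysis* plans a mixed ANOVA of treatment group "x time [baseline, 8-week post-intervention, and 14-week follow-up"]. It does not say which term of that model decides whether treatment worked. *Randomization and blinding* fixes the order of events: "After ensuring study eligibility and completing baseline assessments, the participants will be randomly assigned". *Hypotheses* predicts greater improvement in the experimental group at both 8 and 14 weeks.

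**The concern.** A between-subjects main effect in a repeated-measures ANOVA compares the groups on each participant's average over all visits. Here one of the three visits precedes randomisation, so treatment cannot affect it and the expected difference there is zero. A treatment worth 10 points at weeks 8 and 14 therefore shows up in that average as only two-thirds of 10 points. The power calculation nevertheless assumes about the full 10 points in the average.

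The average is also not what the hypothesis is about. Greater improvement after baseline corresponds to a group-by-time term, or to a baseline-adjusted difference after treatment.

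This is the trial's only power statement. If it is attached to the wrong term and the deciding term is not named, a non-significant result is hard to interpret, because the stated 80% would not describe the chance of detecting an effect the size of the minimal clinically important difference.

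**Working it through.** **Inputs.** From *Sample size calculation*: difference 10 points, SD 12, f = 0.40, m = 3 measures, correlation ρ = 0.5, alpha 0.05, N = 36, dropout 30%, target 46. From *Data analysis*: the visits are baseline, week 8 and week 14. From *Randomization and blinding*: baseline comes before allocation. Assumed, because not stated: 1:1 allocation, SD 12 and the same correlation at all visits, and an equal effect at weeks 8 and 14.

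**1. Reproduce the stated 36.** For the group main effect, λ = N f² m / [1 + (m − 1)ρ] on (1, N − 2) degrees of freedom. With f = 0.40, λ = 36 × 0.16 × 3 / 2 = 8.64 and power is 0.815. At N = 34 power is 0.791, so 36 is the smallest even total that reaches 80%. With f = 0.40, one measure would need 52 and two would need 40, and the interaction option would give power above 0.999 at 36. Only the main effect over three measures yields the stated figure.

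The stated f is slightly rounded: 10/12 = 0.833 and half of that is 0.417 (which would need 34), while f = 0.40 corresponds to 9.6 points at SD 12.

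**2. Same test with no difference at baseline (0, 10, 10).**
- Mean difference: (0 + 10 + 10)/3 = 6.67 points, so f = 6.67/24 = 0.278.
- Variance of a three-visit mean: 144 × (1 + 2 × 0.5)/3 = 96.
- λ = (N/4) × 44.4/96, on (1, N − 2) degrees of freedom.

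A simulation of 100,000 trials gives 51.0% at 36 and 46.2% at 32, in agreement with the formula.

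**3. Group-by-time interaction in the planned 2 x 3 model.** The sum of squared deviations of (0, 10, 10) from its mean is 66.7. λ = (N/4) × 66.7/(144 × 0.5), on (2, 2(N − 2)) degrees of freedom.

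**4. Baseline-adjusted comparisons**, on (1, N − 3) degrees of freedom.
- One post-treatment visit: residual variance 144 × (1 − 0.25) = 108; λ = (N/4) × 100/108.
- Mean of weeks 8 and 14: residual variance 144 × (0.75 − 0.25) = 72; λ = (N/4) × 100/72.

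**Results** (10 points, SD 12, ρ = 0.5; 46 × 0.7 = 32.2, hence 32):

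| Test | 36 analysed | 32 analysed | 46 analysed |
|---|---|---|---|
| Group main effect, three visits | 51% | 46% | 62% |
| Group-by-time interaction (2 df) | 72% | 66% | 83% |
| Baseline-adjusted, one visit | 80% | 75% | 89% |
| Baseline-adjusted, mean of weeks 8 and 14 | 93% | 90% | 97% |

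With 9.6 points instead of 10 (f = 0.40 exactly), the main effect has 48% and 43% at 36 and 32, and the interaction 68% and 62%. For 80% power at 10 points, the main effect would need about 70 analysed.

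**5. Sensitivity to the correlation** (36 / 32 analysed):
- ρ = 0.3: main effect 60% / 55%.
- ρ = 0.7: main effect 44% / 40%, interaction 91% / 88%, baseline-adjusted single visit 93% / 89%.

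**The case against.** The strongest reply is that the low main-effect figures do not describe the trial. The planned analysis is a 2 x 3 group-by-time model, nothing says its main effect will decide, and a hypothesis about improvement leads naturally to the interaction. Baseline as a repeated outcome is conventional, and valid when the interaction or a suitable contrast is read: the contrast of post-treatment mean against baseline has 80% power at 36, the same as a baseline-adjusted comparison at one visit. The intention-to-treat statement includes all 46 randomised, with whom the interaction reaches 83%. A correlation of 0.7 would lift it above 80% even with 32.

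Much of this stands. A reader might infer that a true 10-point effect would be missed about half the time, or that the recruitment target is too small. The documents support neither inference. The first holds only if the main effect decides the trial, which the protocol does not say; if the interaction is read, the miss rate is about 28% to 34% at 36 and 32. The second fails because other tests available from the same data reach 80% at the stated 36.

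The reply does not rescue the power statement. The 80% was computed for the main effect and with an effect at baseline that randomisation rules out in expectation. The interaction falls short at 36 with the protocol's own correlation of 0.5. The figures for 46 are an upper bound, since they need outcome data from everyone while the protocol itself allows for 30% dropout.

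**Conclusion.** The point holds in a limited form. The arithmetic behind 36 is correct for the test chosen; the untenable part is the assumed effect, which puts about 10 points at a visit before randomisation. With a realistic profile, the stated 80% at 36 holds neither for the term it was computed for (about 51%) nor for the interaction that better fits the hypothesis (about 72%). The figures of 46% to 62% belong to the main effect alone and should not be quoted as the power of the trial.

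These numbers rest on 1:1 allocation, SD 12 and correlation 0.5 throughout, and an effect of equal size at weeks 8 and 14. The main-effect conclusion is robust: it stays at 60% or below with 36 analysed for correlations from 0.3 to 0.7. The interaction and baseline-adjusted figures depend more on the correlation and improve as it rises.

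**What to change.** **Data analysis.** Name the deciding SCIM III analysis as the baseline-adjusted group difference after treatment: a mixed model with the 8- and 14-week values as outcomes, baseline SCIM III as covariate, and group, visit and group-by-visit terms. State that the group main effect that includes baseline will not be interpreted as the treatment effect. Say whether the deciding contrast is a single visit or the mean of weeks 8 and 14. The hypotheses name both times, so choosing 8 weeks alone is an option and not a requirement.

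**Sample size calculation.** Replace the present power statement with one for the chosen contrast, for 10 points, SD 12 and correlation 0.5: about 80% with 36 analysed or 75% with 32 at a single visit; about 93% or 90% for the mean of the two visits if the effect is sustained. If a single visit is chosen, acknowledge that 30% dropout from 46 leaves power somewhat below 80%.

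**Cost.** Wording in two sections. Baseline SCIM III is already collected and no additional patients are needed. The change should be dated and recorded before outcome data are examined by group.

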## Discussion

The management of SCI requires considerable health care resources and can impose a significant financial burden on the affected individuals, their families, and the community [26]. This is particularly concerning in resource-constrained regions, such as northern Nigeria, where many SCI victims come from low-socioeconomic backgrounds [27] and experience low QOL [28], in addition to limited or lack of rehabilitation centers [27,29]. This study aims to determine the effects of ULAE plus general exercise program versus general exercise alone among patients with SCI in northern Nigeria. Based on our hypotheses, we anticipate that participants receiving the ULAE plus general exercise will demonstrate significantly greater improvements in RPP, functional independence, BP, and QOL compared to those receiving general exercise alone. Improvements in these outcomes are expected to help the patients return more quickly to their ADL and maintain an adequate level of physical fitness. The primary strength of this study lies in its design as an RCT with some key methodological features. Additionally, the intervention is both accessible and affordable, as the arm ergometer and reciprocal pulley can be improvised at minimal cost.

However, the study has several potential limitations worth noting. First, due to the nature of the interventions, blinding both participants and therapists will not be feasible. Second, although a formal sample size calculation was performed, the trial is powered to detect only a 10% difference in function, as measured by the SCIM III, between the groups, accounting for the anticipated high dropout rate. Third, due to a lack of funding, only a few outcomes will be evaluated in this trial. Any additional limitations observed during the study will be reported in the main trial publication.

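### The dropout allowance is miscalculated: 30% loss from 46 randomised leaves 32, not the 36 the power calculation requires

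*Protocol article*

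**What the plan says.** The Sample size calculation section of the protocol article bases the trial on the total SCIM III score, with a 10-point difference and an SD of 12.0. The test is a repeated-measures, between-subjects ANOVA F-test, with an alpha "level of 0.05; power of 0.80", an "effect size of 0.40 when accounting for 3 repeated measures", and a "correlation among repeated measures of 0.5". This gives 36 participants in total.

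The section then allows for loss. "Accounting for a potential dropout rate of 30" per cent, which it equates with 10 participants, "the final sample size was determined to be 46 participants".

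The limitations paragraph of the Discussion says the trial is powered for a 10% difference on SCIM III, "accounting for the anticipated high dropout rate".

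**The concern.** A dropout rate is a proportion of those who enter the trial, so the number to randomise is the required number of completers divided by one minus the rate. The protocol instead takes 30% of the required completers and adds it on, and rounds down in doing so. The total is then too small for the dropout rate printed beside it.

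At stake is the claim that the trial keeps 80% power at the loss the investigators themselves expect. A reader of a null SCIM III result would rely on that claim. The protocol's Introduction attributes the null findings of previous trials partly to inadequate sample size and lack of follow-up, so the allowance for loss is part of this trial's rationale.

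**Working it through.** **Inputs, all from the Sample size calculation section:** alpha 0.05; target power 0.80; f = 0.40; m = 3 measures; correlation ρ = 0.5; 36 required; dropout 30%, taken as 10; final total 46. Two groups. The allocation ratio is not stated, so 1:1 is assumed.

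**1. Reproduce the 36.** For the between-groups factor in a repeated-measures ANOVA, power comes from the noncentral F distribution with 1 and N − 2 degrees of freedom and noncentrality

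λ = f² × N × m / [1 + (m − 1)ρ] = 0.16 × N × 3 / 2 = 0.24 N.

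| N analysed | λ | Power |
|---|---|---|
| 32 | 7.68 | 0.765 |
| 34 | 8.16 | 0.791 |
| 35 | 8.40 | 0.803 |
| 36 | 8.64 | 0.815 |

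The smallest N reaching 0.80 is 35. With equal groups it is 36, so the stated 36 is reproduced.

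**2. Reproduce the 46.** 36 × 0.30 = 10.8, cut to 10; 36 + 10 = 46. Only this additive rule gives the stated total. Even that rule, rounded up, gives 36 × 1.30 = 46.8, so 47.

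**3. Apply the stated dropout to the stated total.** 46 × 0.30 = 13.8 lost; 46 × 0.70 = 32.2, so about 32 remain. That is 36 − 32 = 4 short.

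**4. Dropout that 46 does cover.** 10 / 46 = 21.7%.

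**5. Size that matches the stated inputs.** 36 / 0.70 = 51.4, so 52, which is 6 more than stated. Check: 52 × 0.70 = 36.4.

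**6. Power at the stated dropout.** With 32 completers power is 0.765 (table above). That is 3.5 percentage points below the stated 0.80 and 5.0 points below the 0.815 given by 36.

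**The case against.** **The effect size was rounded down.** A 10-point difference with SD 12.0 gives f = 10 / (2 × 12) = 0.417, and the protocol uses 0.40. At 0.417, 32 completers give power 0.798, practically the target. This is a fair point and shows how small the practical loss may be. But 0.40 is the effect size the protocol states and the one that produces its 36. The mismatch between 30%, 10 and 46 does not depend on the effect size.

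**The gap to 80% is smaller than four.** Since 35 participants already give 0.803, the shortfall against 80% itself is 3. That is true if groups of unequal size are accepted; against the 36 the protocol requires, it is 4.

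**Intention to treat keeps everyone.** The Data analysis section includes all randomised participants. That label does not supply unobserved outcomes at 8 and 14 weeks, and the article describes no method for them. The sample size section itself treats dropouts as lost and enlarges the trial for them, so that step has to be right on its own terms.

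**The Discussion gives no power figure.** Correct. It is not a second arithmetic error, only a repetition of the claim that dropout has been covered.

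**The power figure is not for the hypothesised comparison.** The planning formula concerns a group effect averaged over three occasions including baseline, while the hypotheses concern 8 and 14 weeks. This stands as a caution on how the 76% is worded. A baseline-adjusted 8-week comparison (10 points, SD 12, correlation 0.5) shows a similar drop, from about 80% with 36 to about 75% with 32. The plan does not specify that analysis, so it is only a side check.

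**Conclusion.** The concern holds. On the protocol's own figures, 46 randomised does not leave 36 completers at 30% dropout. It leaves about 32, with power of about 76.5% rather than 80%. The stated total is sufficient only up to 21.7% loss, and 52 would be needed for 30%.

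The error is certain, because it follows from figures printed in a single section. Its consequence is modest: 4 completers and 3.5 points of power. The power figures assume 1:1 allocation, f = 0.40, three measures and correlation 0.5, and that participants who drop out contribute nothing to the analysis. The head counts in steps 3 to 5 do not depend on the effect size or correlation once 36 is taken as the requirement.

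**What to change.** In the Sample size calculation section, replace the dropout statement with wording such as: *Randomising 46 participants retains the required 36 if dropout is no more than about 22%. At 30% dropout about 32 would complete, giving about 76% power under the planning assumptions.* Make clear that the 76% comes from the same repeated-measures, between-groups calculation that gave the 36.

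In the Discussion, change the limitation so that it no longer implies full power at the expected dropout, and give the 22% figure there too.

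If the recruitment target can still be changed, 36/0.70 = 52 is the size consistent with the stated inputs. The Trial status section gives recruitment opening on 1 February 2023 and final follow-up expected by 30 December 2024, so this may no longer be possible.

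The cost of the main fix is wording only. No analysis changes, and one stated figure becomes slightly less favourable.
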